**Fig. 1 Fig1:**
[figure not shown]
Research flowchart

General information, medical/treatment history, and pre-assessment results of each participant will be confidentially collected by the research assistant before the initial intervention.

Assessments will be conducted before the intervention (T0), before the 5th intervention (T1), immediately after the 8th intervention (T2), and at the 4th week after the end of the 8th intervention (T3), which include the surface EMG evaluation of pelvic floor muscles, NIH Chronic Prostatitis Symptom Index (NIH-CPSI), three-dimensional quantification, shear wave elastography, and the sympathetic skin response.

The primary outcome measurements will be performed at T0, T1, T2, and T3. Secondary outcome measurements will be carried out at T0 and T3.

The SPIRIT figure is displayed in Table 1.

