### Sample size calculation

Previous studies showed that myofascial release therapy had notable effects [32] (corresponding to a Cohen’s *d* of about 0.5) on improving quality of life, prostate-related symptoms, and pain. The primary outcome will be the change in NIH-CPSI scores, the clinical response rate, and the remission rate as measured by the NIH-CPSI 4 weeks after the completed intervention. We assumed that extracorporeal shockwave combined with myofascial release therapy had similar effects on NIH-CPSI scores. A sample of 40 participants per group was computed by the G*power software to achieve a power of 60% and a level of significance of 5% and a 95% confidence level. To compensate for an estimated dropout rate of 25%, 150 participants will be ultimately required. (i.e., the number in each group is 50).

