### Statistical methods

Statistical analysts perform data analysis in a blind state. All statistics analyses will be performed using SPSS 25.0 for Windows (SPSS Inc., Chicago, IL, USA). All data will be entered into SPSS by the research assistant. A *p*-value of < 0.05 will be considered statistically significant. One-way (3 groups: single extracorporeal shockwave therapy vs single myofascial release therapy vs combined therapy) analysis of variances (ANOVA) with repeated measures will be performed to compare changes in sEMG assessment and NIH-CPSI scores between and within groups over different time points (i.e., T0-T2). A paired sample *t*-test was used to compare the differences in outcome indicators between groups at T2 and T3 to determine the long-term efficacy of each intervention. Post hoc analyses will be performed when any significant difference both between- and within-group is found in any of the outcome variables. Bonferroni correction will be used to adjust the alpha levels. Multilevel regression or a generalized estimating equation (GEE) will also be used as a sensitivity analysis to analyze the correlation between NIH-CPSI scores and the results of sEMG assessment of the pelvic floor muscle and the results of sympathetic skin response. Mediation analysis will examine the mediating effect of sEMG assessment at T1 on the relation between extracorporeal shockwave therapy and NIH-CPSI scores at T2. This study strictly controlled for gender, age, and BMI of the participants, which may affect the primary and secondary outcomes. The mean absolute difference (MAD) and standard error of measurement (SEM) will be used to evaluate inter-method reliabilities. Consequently, Bland–Altman plots will be used to investigate the agreement between NIH-CPSI and SSR. Since the two measurement results have different measurement units, a *Z*-score will be calculated based on the formula: *Z*-score = (observation value − mean value)/SD.

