It is now recommended by the British Urology Association that the main aim of CP/CPPS treatment is to mitigate functional damage to patients [42], usually with single internal and external fascia manipulation. However, most of the studies on myofascial release therapy are pre-and post-controlled trials while lacking high-quality randomized controlled trials [43]. As mentioned in the literature review, myofascial release therapy can effectively alleviate the symptoms of pelvic floor pain in patients, but evidence for the intervention efficacy remains greatly inconclusive because the main primary outcome in existing studies is subjective scale [32, 44, 45]. At present, there are no studies on myofascial release therapy combined with extracorporeal shockwave therapy. Our study will compare three treatments—single myofascial release therapy, extracorporeal shockwave therapy, and combined therapy—and then propose to compare the relationship between the three treatment modalities and the subjective and objective functional changes before and after treatment.

In previous assessments, we found that the symptoms of chronic pelvic pain syndrome may be closely associated with increased pelvic floor muscle tone, which can be effectively reduced with myofascial release therapy. In this study, by comparing the association between the primary and secondary outcome measure and different therapy modalities (extracorporeal shockwave, myofascial release, and combined therapy) on the therapeutic effect of pelvic floor hypertonia at T0-T3 stage, it was proposed to determine (1) if shockwave therapy can reduce pelvic floor muscle tension further after taking myofascial release therapy; (2) if the combined therapy can reduce pelvic floor muscle tone, relieve the discomfort symptoms, and improve the quality of life of the patients more efficiently and have a long-term effect than single treatment [46, 47]; (3) if curative effect can be reflected by the change of sympathetic skin response before and after treatment; and (4) if there exist other mechanisms that may improve the symptoms of patients other than what extracorporeal shockwave and myofascial release therapy did on reducing pelvic floor muscle tone.

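### The trial is sized on NIH-CPSI at T3, but the three-arm ANOVA ends at T2, and the only test given to T3 is a paired t-test that cannot compare randomised arms

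*Protocol article*

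**What the plan says.** **Sizing visit.** Sample size calculation takes as primary outcome the change in NIH-CPSI, the response rate "and the remission rate as measured by the NIH-CPSI 4 weeks after the completed intervention". Study design (text under Fig. 1) places the last assessment "and at the 4th week after the end of the 8th intervention (T3"), so the sizing visit is T3. The assumed effect is a Cohen's d "of about 0.5) on improving quality of life, prostate-related symptoms, and pain", with 40 per group for 60% power at the 5% level, raised to 50 per group for dropout.

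**Visit schedule.** Study design states: "The primary outcome measurements will be performed at T0, T1, T2, and T3".

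**Main analysis.** Statistical methods plans a three-group ANOVA with repeated measures "to compare changes in sEMG assessment and NIH-CPSI scores between and within groups over different time points (i.e., T0-T2").

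**Analysis of T3.** The next sentence of Statistical methods covers T3 with a test for paired data: "t*-test was used to compare the differences in outcome indicators between groups at T2 and T3 to determine the long-term efficacy of each intervention".

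**Question asked.** The Discussion speaks of therapy effects over T0 to T3 and asks whether combined therapy can work "more efficiently and have a long-term effect than single treatment".

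**The concern.** The visit that fixes the sample size lies outside the window of the only suitable between-arm test. The test that does reach T3 is of the wrong kind. A paired t-test needs two measurements on the same patient, so here it can only say whether patients improved or relapsed between T2 and T3. It cannot say whether one randomised arm did better than another at T3.

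Two things are at stake. A benefit of combined therapy that emerges or persists at four weeks might never be tested between arms. Conversely, an end-of-treatment difference that has gone by T3 could be reported as the main result of a trial sized on T3. The text also leaves room to choose between T2 and T3 after the data are seen.

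**Working it through.** **1. Reproduce the plan's figure.** Inputs from Sample size calculation: d = 0.5, power 60%, alpha 5% (sidedness not stated).
- Two-sided comparison of two means: n = 2(z₀.₉₇₅ + z₀.₆₀)²/d² = 2(1.960 + 0.253)²/0.25 = 39.2, so 40 per group.
- With the non-central t distribution, the power at 40 per group is 59.8%, and 41 are needed to reach 60%.
- A one-sided test would need 29 and does not fit.

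The stated 40 is therefore a two-group comparison at a single visit, and the text places that visit at T3.

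**2. Look for a between-arm test at T3 in Statistical methods.**

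| Planned analysis | Visits | Compares arms at T3? |
|---|---|---|
| Repeated-measures ANOVA | T0 to T2 | No, T3 is not in the model |
| Paired t-test | T2 and T3 | No, it is a within-patient contrast |
| Post hoc tests with Bonferroni | No visit named; conditional on a significant result | Not stated |
| Multilevel regression or GEE | Not stated | No, assigned to correlations between measures |
| Mediation analysis | T1 and T2 | No |

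**3. What the ANOVA window costs.** Assumptions: 40 per arm, three arms, SD 1, equal between-visit correlation ρ = 0.5, and one arm differing by d = 0.5 at T3 only. For the group-by-time test the non-centrality is λ = n × (sum of squared interaction terms)/(1 − ρ).
- T0 to T2: all interaction terms are zero, so λ = 0 and the rejection rate is alpha, 5%, whatever ρ is. A simulation of 4,000 runs gave 5.3%.
- T0 to T3: the sum is d²(1 − 1/3)(1 − 1/4) = 0.25 × 0.667 × 0.75 = 0.125, so λ = 40 × 0.125/0.5 = 10. With (3 − 1)(4 − 1) = 6 and (120 − 3)(4 − 1) = 351 degrees of freedom, the power is 63% (simulation 65%).
- The same formula gives λ = 7.1 and 47% at ρ = 0.3, and λ = 16.7 and 88% at ρ = 0.7.
- One-way ANOVA of the T0-to-T3 change: λ = 40 × 0.25 × 0.667/(2 × 0.5) = 6.67 on 2 and 117 degrees of freedom, 62% (simulation 63%).

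**4. The reverse case (illustration).** Suppose one arm differs by 0, 0.25 and 0.5 SD at T0, T1 and T2 and by nothing at T3, with ρ = 0.5. The T0-to-T2 group-by-time test rejects in 50% of runs, although no difference remains at T3.

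**5. A single arm pair at T3.** With 40 completers per arm and d = 0.5, the two-sided t-test has 59.8% power at alpha 5%, and 42% at 0.05/3 for three pairs. At 25% dropout from 50 (37 to 38 completers), the unadjusted power is 56% to 58%.

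**The case against.** The strongest defence is that the plan does deal with T3. Directly after the ANOVA it gives T2 and T3 a test of their own, described as between groups and aimed at long-term efficacy. A reader might infer from the T0-to-T2 window that T3 is left out altogether, and that would be wrong. What does not stand is the tool: pairing is not possible across independent arms, so the sentence states an intention that its test cannot carry out.

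The window may also be a slip for T0 to T3, since the Discussion uses the longer range. That is plausible, but the current text still conflicts with itself. It also stands that only Sample size calculation ties the primary outcome to T3; other sections list the visits without ranking them. T3 is thus the visit used for sizing rather than one declared primary throughout.

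A reader might further infer that including T0 as a level of the ANOVA dilutes the arm effect. For a difference of 0, 0.25 and 0.5 SD over T0 to T2, the group effect averaged over visits has only 24% to 33% power at correlations from 0.7 down to 0.3. The document does not support that reading. It plans to compare changes, which is the group-by-time interaction, and T0 is the reference for that test. Its power under the same assumptions is about 37%, 50% and 73% for two arms at correlations 0.3, 0.5 and 0.7. Likewise, not using T0 as a covariate is not an error: adjustment can add precision, but repeated-measures ANOVA with T0 as a level is a conventional analysis of change.

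**Conclusion.** The point holds as a contradiction between Sample size calculation, Statistical methods and the Discussion. No valid between-arm test is named at T3. For a difference confined to T3, the planned ANOVA has 5% power, and this figure depends on no assumed correlation. With T3 included, the group-by-time test has about 63% power at ρ = 0.5, and 47% to 88% over ρ = 0.3 to 0.7. Those figures assume 40 per arm, one arm differing by 0.5 SD, and equal correlation between visits; the correlation is not given in the protocol. The T3-only and fading patterns are illustrations, not forecasts. The contradiction needs to be corrected before analysis because it concerns the primary comparison.

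**What to change.** In Statistical methods:
- Extend the repeated-measures model to T3. One suitable form is a mixed model with T1, T2 and T3 as outcomes and arm, visit and arm-by-visit as effects. Adding the T0 value as a covariate is an optional gain in precision.
- Name the between-arm difference in NIH-CPSI at T3 as the primary comparison for all three arm pairs, with the Bonferroni correction already stated. Differences at T1 and T2 become secondary.
- Replace the paired t-test with that T3 contrast. If T2-to-T3 change within an arm is still of interest, label it as descriptive of durability.

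If the sponsor in fact intends end of treatment as the primary visit, Sample size calculation and the Discussion should be aligned to T2 instead; either way, one visit should be named.

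The cost is wording. T3 is already scheduled for the primary outcomes, and the planned number of patients does not change. The sponsor should note that three Bonferroni-adjusted pairs at T3 have about 42% power each with 40 completers per arm and d = 0.5, before any gain from baseline adjustment.

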## Methods and analysis

### Study design

The proposed study will be a three-group randomized control trial (RCT) design that includes 150 participants from Zhongda Hospital Affiliated to Southeast University, with equal allocation of participants to the three intervention groups. The research flow chart is shown in Fig. 1. The reporting of this protocol is strictly based on the Standard Protocol Items: Recommendations for Interventional Trials (SPIRIT), which is found in Additional file 1.

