### Sequence generation

Randomization 1:1:1 is done using https://www.sealedenvelope.com/simple-randomiser/v1/lists with varying block randomization with a block size of 6. No stratification is used.

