### Recruitment

When all criteria for participation are met, the patient can consider participation and ask questions to any therapist. If a patient decides to participate in the trial, the patient signs an informed consent form. Subsequently, the patient will be allocated to one of the three groups. Participants cannot switch from the extracorporeal shockwave, myofascial release, and combined therapy groups. However, a patient is allowed to withdraw from the trial without providing a reason for withdrawal and still receives usual care.

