## Data collection and management

### Plans for assessment and collection of outcomes

Three groups of participants will be treated by trained therapists, and the intervention process will be strictly in accordance with the study protocol. The Primary outcome measurements will be carried out at T0, T1, T2, and T3. Secondary outcome measurements will be carried out at T0 and T3. Equipment used in the assessment, such as pelvic floor biofeedback electrostimulation, pelvic floor ultrasound, and sympathetic skin response devices, will be operated by the same researchers, and the type of equipment and the assessment site will remain the same.

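### The only efficacy test assigned to T3 is a paired t-test between independent arms, so no sound arm comparison is specified at the 4-week follow-up

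*Protocol article*

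**What the plan says.** All references are to the protocol article.

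- **Statistical methods.** The repeated-measures ANOVA compares sEMG and NIH-CPSI "between and within groups over different time points (i.e., T0-T2". T2 and T3 are then given to a different test: "A paired sample *t*-test was used to compare the differences in outcome indicators between groups at T2 and T3". Its purpose is "to determine the long-term efficacy of each intervention".
- **Design.** The trial is randomised "with equal allocation of participants to the three intervention groups" (Study design). On the allocation list, "No stratification is used" (Sequence generation). Patients stay in one arm: "Participants cannot switch from the extracorporeal shockwave, myofascial release, and combined therapy groups" (Recruitment).
- **Timing.** The last assessment is "at the 4th week after the end of the 8th intervention (T3" (Study design, text under Fig. 1). The sample size section places the primary NIH-CPSI outcome at this same point, 4 weeks after treatment ends.
- **Secondary outcomes.** "Secondary outcome measurements will be carried out at T0 and T3" (Plans for assessment and collection of outcomes), so they have no T2 value.
- **Question asked.** The Discussion wants to know whether combined therapy has a longer-lasting effect than either single therapy, which is a between-arm question.

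**The concern.** A paired t-test needs a partner for each observation. Here a patient in one arm has no partner in another, because the arms are neither matched nor crossed over. The sentence therefore names a test that does not fit the comparison it describes.

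If the sentence is read as T2 versus T3 within each arm, the pairing is real, but the result is three separate statements about change after treatment and no comparison of treatments.

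At stake is the efficacy conclusion at T3. The sample size section names that point for NIH-CPSI and the Discussion's long-term question turns on it, yet the ANOVA stops at T2.

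**Working it through.** **1. What the trial was sized on.** Inputs from the sample size section: Cohen's d about 0.5, 40 per group, 5% significance, 60% power. Taken two-sided, an independent two-sample t-test has power 0.598 at n = 40 per group, which reproduces the stated 60%. A paired t-test with standardised difference 0.5 and n = 40 would have 0.869. The sizing therefore rests on an independent-groups comparison.

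**2. Paired test across arms.** With n per arm, mean difference D and arm SDs of 1, the paired statistic is t = D / √[(2 − 2r)/n], where r is the sample correlation created by whatever order the rows happen to be in. Its expected value is zero, but in any one ordering it is not zero.

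Take n = 40 and D = 0.45:

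- Independent test: t = 0.45/√(2/40) = 2.012 on 78 df, p = 0.048.
- Paired, r = 0: t = 2.012 on 39 df, p = 0.051.
- Paired, r = +0.5: t = 0.45/√(1/40) = 2.846, p = 0.007.
- Paired, r = −0.5: t = 0.45/√(3/40) = 1.643, p = 0.108.

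In a simulated data set with these means and SDs, 5,000 random re-pairings gave p from 0.005 to 0.109, with 48% below 0.05. The patients and values were the same each time; only the row order changed.

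Over 20,000 simulated trials at n = 40, the type I error was 0.049 for both the paired and the independent test. Power at d = 0.5 was 0.587 and 0.598. The error rate is not inflated and little power is lost. The fault is that the result for a given data set is not defined. In addition, the plan expects 25% dropout, and if completer numbers differ between arms, some patients have no partner and cannot be used.

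**3. Paired test within each arm (T2 versus T3).** Suppose one arm is 0.5 SD better than another at both T2 and T3, with n = 40. In simulation the within-arm test rejected in about 5% of runs in either arm (0.047 to 0.053, for assumed correlations of 0.3 to 0.7). It cannot see a sustained advantage.

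Now suppose all three arms have the same true T2-T3 change, and arms are contrasted by which p falls below 0.05. Let p be the power of one paired test. The chance that the three arms do not all agree is 1 − p³ − (1 − p)³. Take n = 38 (50 × 0.75 = 37.5, rounded up) and alpha 0.05. The size of change, in SDs of the change, is assumed because the protocol gives none.

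| True change | Power p | Three arms fail to agree |
|---|---|---|
| 0 | 0.050 | 14% |
| 0.1 | 0.092 | 25% |
| 0.2 | 0.225 | 52% |
| 0.33 | 0.509 | 75% |
| 0.5 | 0.851 | 38% |

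**4. Secondary outcomes.** The test is applied to outcome indicators without naming them. If these include elastography, hiatal dimensions and SSR, it cannot be run, since none of them has a T2 value.

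**5. What a direct comparison would give.** Assume 40 per arm and a 0.5 SD arm difference at T3. ANCOVA on the T0 value then has power 0.63, 0.71 or 0.87 for a T0-T3 correlation of 0.3, 0.5 or 0.7 (assumed range). The unadjusted independent t-test has 0.60. With Bonferroni over three pairs, the ANCOVA figures are 0.46, 0.54 and 0.75.

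**The case against.** The best defence is that the sentence is loosely worded: a within-arm T2-T3 test was meant, as its stated purpose about each intervention suggests, and such a test is legitimate. That stands as far as it goes. The test is a reasonable description of durability and need not be deleted. It still leaves the between-arm question at T3 without an analysis. The Discussion does speak of comparing the therapies over T0-T3, but that is an intention, and the methods section does not carry it out.

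Several stronger readings are tempting and are not supported:

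- **That T3 data are used nowhere else.** The analysis relating NIH-CPSI to SSR and the Bland-Altman analysis of the two also draw on T3, because SSR is measured only at T0 and T3. These are association and agreement analyses, so the paired t-test is the only specified efficacy test using T3.
- **That arbitrary pairing produces false positives.** It does not (step 2). Halving the degrees of freedom is also a minor matter.
- **That the plan will read a non-significant T2-T3 result as maintained benefit, or rank arms by p-value.** No passage says so. It is a risk that the within-arm reading leaves open.
- **That 75% disagreement is typical.** It is the maximum, reached where power is about one half. The plan's Bonferroni correction, whose scope is not stated, would alter the figures if it covered the three within-arm tests: at alpha 0.0167 the no-change case falls to 5% and the 0.33 case to 66%.
- **That the test is certainly meant for the secondary outcomes.** The preceding sentence names only sEMG and NIH-CPSI, both measured at T2 and T3, so the point in step 4 is conditional.

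**Conclusion.** The plan is wrong as written. A paired t-test is assigned to a between-group comparison of independent, unmatched arms, and the ANOVA that could have compared them stops at T2. On one reading the p-value depends on row order (about 0.005 to 0.11 in the example). On the other the test is valid but compares no arms. Neither gives a sound arm comparison of NIH-CPSI at the 4-week follow-up or answers the Discussion's long-term question.

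That conclusion follows from the text and needs no numerical assumption. The 14% to 75% range does: it assumes an equal true change of 0 to 0.5 SD in every arm, 38 per arm, alpha 0.05 per test, and a reader who contrasts arms by significance. It shows the size of a risk and does not predict what the trial will report.

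**What to change.** In Statistical methods:

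1. Extend the planned repeated-measures analysis to T3, or use a baseline-adjusted mixed model, with a group-by-time term. Pre-specify the between-arm contrasts at T3, each with a 95% confidence interval, and say how the Bonferroni correction applies to them.
2. For outcomes measured only at T0 and T3, use ANCOVA of the T3 value on arm and T0 value.
3. If a paired T2-T3 test is kept, reword it as a within-arm description, remove the reference to groups, and state which outcomes it covers.

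No extra patients, visits or measurements are needed. The cost is a change of wording and a little more analysis. Under the assumptions in step 5, the baseline-adjusted comparison has at least the power of the unadjusted test the trial was sized on.

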**Methods:**

The proposed study will be a three-group randomized control trial (RCT) design that includes 150 participants from Zhongda Hospital Affiliated to Southeast University, with equal allocation of participants to the three intervention groups. The study duration will be 8 weeks, which includes a 4-week treatment period and a 4-week follow-up period. The primary outcome will be the changes in surface electromyography (sEMG) assessment and National Institutes of Health-Chronic Prostatitis Symptom Index (NIH-CPSI). The secondary outcomes will include the changes in three-dimensional quantification, shear wave elastography (SWE), and sympathetic skin response (SSR) testing. Assessments will be conducted before the intervention (T0), before the 5th intervention (T1), immediately after the 8th intervention (T2), and the 4th week after the end of the 8th intervention (T3).

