### Study setting

This trial (NCT05659199—ClinicalTrials.gov) is a monocenter randomized controlled trial with three groups conducted in Department of Rehabilitation and the Department of Ultrasonography of Zhongda Hospital, Nanjing, Jiangsu, China. Zhongda Hospital is a teaching hospital, where the total number of outpatients annually is 2.03 million. The Zhongda Hospital has a dedicated Pelvic Floor Health Management Centre to assess, treat, and follow-up patients with pelvic floor dysfunction. Patients admitted to the Pelvic Floor Health Management Center include those seeking postpartum pelvic floor rehabilitation, those with chronic pelvic pain syndrome, and others with pelvic floor dysfunction. Treatment provided by the Pelvic Floor Health Management Center includes pelvic floor biofeedback electrostimulation, pelvic floor magnetic stimulation, extracorporeal shockwave therapy, and myofascial release therapy. Myofascial release therapy is a kind of manipulation therapy. Between 2020 and 2023, more than 1000 patients with pelvic floor dysfunction were treated at the Pelvic Floor Health Management Center. In this trial, the subjects included will be randomly assigned to the extracorporeal shockwave, myofascial release, and combined therapy groups.

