### Eligibility criteria

Patients with hormone abnormalities are excluded because thyroid dysfunction and testosterone may affect prostate function and myofascial status.

Participants will be screened using the following criteria.

Inclusion criteria:According to the National Institutes of Health classification of prostatitis [29], all male patients meet the diagnostic criteria for chronic prostatitis type IIIB/chronic pelvic pain syndrome (pain in the bladder, groin, perineal area, genitalia or lower abdomen with no significant abnormalities on urological examination);Patients are aged 20–40 years;Patients with chronic pelvic pain lasting over 6 months;Patients sign the informed consent form.

Exclusion criteria:Patients with significant coagulation disorders, perineal anatomical abnormalities, hormonal abnormalities, and neurological abnormalities;Patients with an apparent cause of pelvic pain, such as a history of previous surgery, chronic infection, trauma, prostatitis, and epididymitis;Patients receiving other treatments during the study;Patients with any urethral pathology;Patients who have had closed lumbar injections and previous lumbar surgery within 6 months;Patients with other conditions causing pelvic pain;Patients with contraindications to physiotherapy;BMI > 22.9

Termination and shedding criteria:Other serious illnesses occur in the course of treatment;Poor patient adherence and failure to complete the full course of treatment.

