#### Extracorporeal shockwave pseudo-therapy

A plastic film is placed over the treatment head, so the ultrasound waves cannot act on the treatment area.

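### The paired T2–T3 test cannot show long-term efficacy of each intervention; the trial supports between-arm differences 4 weeks after treatment

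*Protocol article*

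**What the plan says.** All references are to the protocol article.

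- **Test and purpose (Statistical methods).** "A paired sample *t*-test was used to compare the differences in outcome indicators between groups at T2 and T3", and the stated purpose is "to determine the long-term efficacy of each intervention".
- **Other analysis of treatment effect (Statistical methods).** The repeated-measures ANOVA for sEMG and NIH-CPSI is given the time points T0 to T2. T3 is outside it.
- **Follow-up (Abstract, Methods).** "The study duration will be 8 weeks, which includes a 4-week treatment period and a 4-week follow-up period". T2 is immediately after the eighth session and T3 is in the fourth week after it.
- **Arms (Study setting).** "the subjects included will be randomly assigned to the extracorporeal shockwave, myofascial release, and combined therapy groups".
- **Pseudo-therapies (under Blinding).** One is described for each modality; for shockwave, "A plastic film is placed over the treatment head, so the ultrasound waves cannot act on the treatment area". The text does not say which patients receive them, and no sham-only arm is listed.
- **Primary time point (Sample size calculation).** The NIH-CPSI outcome is placed 4 weeks after treatment ends.
- **Second long-term statement (Discussion, second numbered question).** Whether combined therapy can "improve the quality of life of the patients more efficiently and have a long-term effect than single treatment".

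**The concern.** The sentence asks one test to carry three claims: that the result is long-term, that it is efficacy, and that it belongs to each intervention separately. A comparison of two post-treatment readings 4 weeks apart supports none of them.

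Followed as written, a stable score from T2 to T3 could be reported as lasting efficacy of shockwave, of release or of the combination, even in an arm where nothing was gained by T2. A further fall from T2 to T3 could be credited to the therapy when it is natural course, regression to the mean or non-specific response.

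The time point also matters. The sample size section makes 4 weeks after treatment the primary time point for NIH-CPSI, and this sentence is the only treatment-effect analysis in Statistical methods that names T3.

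**Working it through.** **1. The horizon.** Treatment lasts 4 weeks and follow-up 4 weeks: 4 + 4 = 8 weeks in total. The last reading is 4 weeks after the last session, and nothing is collected later. Any statement beyond 4 weeks is extrapolation.

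**2. What a paired T2–T3 test estimates.** Write the mean in arm *g* at time *t* as

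mean(*g*,*t*) = baseline + N(*t*) + E(*g*,*t*),

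where N is the non-specific change common to all arms (natural course, regression to the mean, general response) and E is the effect of the arm's treatment. The paired test estimates

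[N(T3) − N(T2)] + [E(*g*,T3) − E(*g*,T2)].

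Baseline drops out. Take N(T3) = N(T2):

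- effect fully maintained, E(*g*,T3) = E(*g*,T2): expected change 0;
- no effect ever, E = 0 at both times: expected change 0.

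The two cases cannot be told apart. If N is still moving, the test picks that up as well.

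**3. How often non-specific change alone would give significance.** The article gives no figure for natural course or placebo response, so this step rests on assumed values. Inputs: no change in E; *n* = 40 per arm, the article's number before dropout; two-sided 5%. The noncentrality is *s*√*n*, with *s* the non-specific change in SDs of the change score and √40 = 6.32.

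| assumed *s* | *s*√40 | paired test rejects |
|---|---|---|
| 0.2 | 1.26 | 23% |
| 0.3 | 1.90 | 46% |
| 0.5 | 3.16 | 87% |

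If the same non-specific change occurs in every arm, it cancels in a between-arm comparison, which then rejects at its nominal 5%.

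**4. The words about groups.** A paired t-test pairs two readings on the same patient. Patients in different randomised arms are not paired, so the named test cannot compare arms. There are two possible repairs:

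- Comparing T2–T3 changes between arms still omits baseline. Two arms with unequal but stable effects would both show zero change.
- Comparing arms at T3 is informative, but needs a test for independent groups.

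**5. Which outcomes the test could cover.** Study design and the data collection section both put the secondary outcomes at T0 and T3 only. On that schedule they have no T2 value, so a T2–T3 test cannot be run on them.

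**6. What the trial is sized for.** With *d* = 0.5, two-sided 5% and 60% power,

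*n* = 2(1.960 + 0.253)² / 0.5² = 2 × 4.90 / 0.25 = 39.2, rounded up to 40 per group.

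This reproduces the article's 40 (power at 40 is 0.609 by the normal approximation, 0.598 by the *t* distribution). That formula is for a difference between two groups, not for a within-arm test.

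**7. What randomisation identifies at T3.** The between-arm difference is E(*a*,T3) − E(*b*,T3), because N cancels. Combined minus single therapy is therefore estimable at 4 weeks. E for a single therapy on its own, against no treatment, is not, because no arm has E = 0.

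**The case against.** The strongest reply is that the trial is comparative. The Abstract, the first aim in the Background and the Discussion all ask which therapy does better, and active comparators suit that question. If each single-therapy arm also receives the other modality's pseudo-therapy, which is a natural reading of the Blinding section but is not stated, combined versus shockwave alone becomes a sham-controlled test of adding release, and likewise for adding shockwave. The disputed sentence speaks of groups, the follow-up length is stated openly, and the Discussion question is already between arms.

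Most of this stands. A reader might infer that without an untreated arm the design can support no efficacy conclusion at all. The article does not bear that out: randomised contrasts at T3 are valid, and only efficacy against no treatment is out of reach. In the Discussion only the word long-term needs changing.

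A reader might also judge 4 weeks too short against the entry criterion, "Patients with chronic pelvic pain lasting over 6 months", or the 12-month quality-of-life finding in the Background. Neither is a follow-up standard. The first is a diagnostic threshold; the second concerns psychological factors associated with quality of life. The Background's mention of good long-term shockwave outcomes gives no duration, and the article has no figure for when an effect would fade. The point is the label, not a required length.

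What the reply does not rescue is the sentence itself. Its test is not a between-group test, and its stated purpose is efficacy of each intervention.

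**Conclusion.** Wrong as written, in a limited sense. The analysis named for T3 cannot deliver its stated purpose: it omits baseline, does not compare arms, and reaches only 4 weeks past treatment. A maintained effect and no effect have the same expected result, zero change. That follows from the form of the test, given only that non-specific change between T2 and T3 is nil. The rates of 23%, 46% and 87% depend on assumed non-specific changes and illustrate the risk when it is not nil; they are not estimates for this population.

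The design, the arms and the number of patients are not faulted on this point. The supportable conclusion is a difference between arms 4 weeks after treatment.

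**What to change.** 1. **Statistical methods.** Replace the paired t-test with a between-arm comparison at T3, adjusted for the T0 value, of the outcomes measured at both T0 and T3. For sEMG and NIH-CPSI this can be done by extending the repeated-measures model to T3; for outcomes measured only at T0 and T3, an analysis of covariance of the T3 value on arm and T0 value would serve.
2. **Same sentence.** State the purpose as estimating the between-arm difference 4 weeks after treatment, and label within-arm T2–T3 changes as descriptive only.
3. **Discussion, second numbered question.** Change the long-term wording to *effect 4 weeks after treatment*.

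No extra arm, visit or patient is needed. The cost is redrafting the text, specifying one model, and giving up the more ambitious claim.
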